### Randomization

The study comprises two study arms – one intervention and one control arm. A cluster unit was defined as a district in this study. Twenty-one districts were, therefore, eligible to be part of the study. Overall, 17 clusters fulfilled the inclusion and exclusion criteria; however, the regional capital was excluded from the selection process to avoid selection bias as its regional hospital is the highest referral point in the region. Sixteen clusters were, therefore, randomized as shown in the trial flow chart (Fig. 2). Cluster randomization was preferred over individual randomization to avoid contamination both at the health professional and client levels, which may occur as a result of social interaction. Randomization was performed by an independent data analyst in order to achieve comparability and avoid selection bias. Randomization was carried out using STATA version 11.0 statistical software. Due to the nature of this intervention, masking was not feasible.

**Fig. 2 Fig2:**
[figure not shown]
Trial flow chart showing cluster selection, assignment and timelines of the cluster randomized controlled trial (CRCT). Clusters that fulfilled the inclusion and exclusion criteria were randomized into eight control and eight intervention clusters. The CRCT started in August 2015 and ends in January 2017.  Activity, *purple oblong*; Timeline. 
*orange oblong*.

### Sampling of clusters for quality of care study

One well-resourced and one poorly resourced cluster will be purposively selected from each study arm. The selection criteria will be based on the number and mix of health facilities in the district and the midwife to number of deliveries (per annum) ratio in a district. While purposive selection of these study districts does not allow generalizability of findings, application of these qualitative methods provides insight into how and why the intervention worked or not.

### The intervention

The intervention is a clinical decision-making support system consisting of an Unstructured Supplementary Service Data (USSD)-based text messaging of standard emergency obstetric and neonatal protocols to providers on their request, based on the results of a formative study previously conducted in the Greater Accra region [37]. As a reference guideline the national Safe Motherhood Protocol (SMP) [36], an elaborate tool that provides detailed state-of-the-art guidelines for maternal and newborn care, ranging from prenatal care, through antenatal, delivery, postpartum and newborn care, was chosen. A committee of medical experts designed concise and precise protocols with respect to word limits using the USSD system and short protocols using USSD templates have been generated. Access to the USSD platform will be limited to a closed user group (intervention group) who will be provided with subscriber identity module (SIM) cards and cell phones by the research team to avoid contamination. To support the use of the USSD-based text messaging system by health care providers, health care providers in the intervention districts will receive monthly reminders via short messaging service (SMS) on the applicability of the text messaging system for clinical decision-making.

Text messaging based on the USSD system was chosen as a low-cost, easily accessible and instant way of requesting needed information during routine and emergency situations by the health care provider to enhance clinical decision-making. To access the USSD platform, health care workers send a text to a specified short code and this assists in the rapid sharing of the needed information. Access to the USSD platform is free and unlimited. The USSD platform is linked to the general electronic data platform of a telecommunication company whose policy and practice assures 99.99% availability of the general electronic data platform. However, availability of phone reception to assess the network may differ according to location of health facilities.

## Monitoring

Uptake of the intervention will be monitored by the frequency of intervention usage using data about requests made to the USSD collected by the telecommunication company providing technical support for the USSD. All health facilities in the intervention arm will be visited periodically to assess the functionality of the intervention on site. Research assistants (in this case, district health information officers have been recruited) will be trained to supervise data collection activities in the non-hospital facilities in all clusters and to provide updates concerning challenges providers may face with the use of the USSD platform to the research team. The supervisory role of the district health information officers includes ensuring that documentation from the non-hospital facilities is complete and collation of completed data collection forms for submission to the project team. The district health information officers will not make any changes to what is recorded on the completed forms. Thus, they will not assess morbidity or mortality causation.

## Data collection

Data about district and facility characteristics in both arms of the study using a structured questionnaire will be collected. These include human and logistical resources, ANC attendance, number of deliveries, obstetric and neonatal admissions, and primary and secondary outcomes at the baseline and at the end of the study.

The impact of the intervention will be evaluated by extraction of data of outcome measures of interest from the district health information management system-2 (DHIMS-2) database which has been shown to provide reliable estimates of measures [46, 47]. This study will assess the effect of a CDMSS on the commonest causes of neonatal and maternal morbidity and mortality in Ghana. Protocols for diagnosis of these conditions are standardized by the Ghana Health Service across the different categories of health facilities, hence diagnosis across facility type are similar. We assume that health care workers make accurate diagnosis of these common sources of morbidity most of which diagnosis can be made using physical examination and rapid diagnostic tests. The diagnoses made by these health care workers across the different categories of health facilities forms the basis of data entered in the DHIMS-2. Details of all the outcome measures the CRCT seeks to extract from the DHIMS-2; however, covers only hospital data. The non-hospital health facilities report only aggregate data through their district health directorate into the DHIMS-2. Details of outcome measures of interest to the CRCT will, therefore, be collected at the facility level for non-hospital facilities participating in the trial. The diagnosis will be based on what is recorded in the DHIMS-2 or what is recorded in the facility health record books by the health care providers as these diagnoses are expected to follow the standard case definitions for Ghana. Availability of network connectivity in health facilities will be measured during the postintervention evaluation using a Likert scale administered to the health care providers.

The QOC of neonatal and maternal health care services will be assessed by measuring health provider adherence to the standard emergency protocols at baseline and at the end of the study. Provider adherence to these protocols for common neonatal and maternal conditions will be assessed using a checklist based on the SMP in use in Ghana. Qualitative assessment (focus group discussions and key informant interviews among health care workers) as to how the intervention was used and why it produced the effects observed will be conducted in the two intervention districts where the QOC study will be conducted.

All data will be collected in an anonymous format. Double entry of data collected will be done and data will be handled in accordance with Good Clinical Practice. Figure 3 summarizes the schedule of enrollment and time points for assessments for this study.

**Fig. 3 Fig3:**
[figure not shown]
Schedule of enrollment, intervention allocation and assessment using Standard Protocol Items: Recommendations for Interventional Trials (SPIRIT) figure for study protocols

## Outcome measures

Institutional neonatal mortality will be considered as the primary outcome measure for this study. For this study neonatal mortality is defined as death of a newborn occurring from birth up to the 28th day of life [12]. Multiple secondary outcome measures pertaining to maternal and neonatal outcomes will also be measured. Aggregate data on primary and secondary outcomes will be extracted from (DHIMS-2) and health facility health record books for non-hospital facilities (Table 1).

**Table 1 Tab1:** Data sources for outcome measures

Outcome measure	Source of data			
	Hospital	Health centre	CHPS	Maternity home
Number of cases of birth asphyxia	DHIMS-2	Facility	Facility	Facility
Number of cases of low birthweight	DHIMS-2	Facility	Facility	Facility
Number of cases of neonatal jaundice	DHIMS-2	Facility	Facility	Facility
Number of cases of neonatal sepsis^a^	DHIMS-2	Facility	Facility	Facility
Number of cases of PIH/pre-eclampsia/eclampsia	DHIMS-2	Facility	Facility	Facility
Number of cases of postpartum hemorrhage	DHIMS-2	Facility	Facility	Facility
Number of cases of prolonged labor	DHIMS-2	Facility	Facility	Facility
Number of cases of puerperal sepsis	DHIMS-2	Facility	Facility	Facility
Number of cases of neonatal deaths	DHIMS-2	Facility	Facility	Facility
Number of cases of maternal deaths	DHIMS-2	DHIMS-2	DHIMS-2	DHIMS-2
Total number of deliveries	DHIMS-2	DHIMS-2	DHIMS-2	DHIMS-2
Total number of ANC attendants	DHIMS-2	DHIMS-2	DHIMS-2	DHIMS-2

^a^Cord sepsis used as a proxy for neonatal sepsis in this study; *ANC* antenatal clinic, *CHPS* Community-based Health Planning and Services, *DHIMS-2* District Health Information Management System-2, *PIH* pregnancy-induced hypertension

## Statistical analysis

Data analysis and reporting will be in line with the Consolidated Standards of Reporting Trials (CONSORT) Statement guidelines [48]. In this study, randomization was done at the district level and not at the health facility level. All health facilities within a district, therefore, form a cluster. Clusters may differ slightly in their characteristics as can be seen in the larger number of non-hospital health facilities in the control arm (Table 2). We will conduct descriptive analysis of both intervention and reference groups at baseline to explore potential differences in study baseline characteristics of clusters and participants in both study arms. To assess the risk of imbalance in baseline characteristics among the clusters, we will use the c-statistic of the propensity score model of the study. The c-statistic of the propensity score model of the study is considered an appropriate tool to detect baseline imbalance in CRCTs where sample size is large and when a large number of covariates are measured [49]. Any observed imbalance in the baseline characteristics of clusters will be adjusted for in the statistical analysis.

The effect of the CDMSS on primary and secondary outcomes will be analyzed based on the principle of intention-to-treat to minimize over-estimation of the effect of the intervention. Logistic regression will be applied to investigate the effect of CDMSS on all outcome measures considering a potential clustering effect of the CRCT design and adjusting for potential confounders. Results will be reported as relative risks with corresponding 95% confidence intervals. A two-tailed statistical significant level of 0.05 will be used. Among clusters in the intervention arm, descriptive analysis of the availability of network connectivity in health facilities will be done and any significant difference in network availability will be adjusted for using logistic regression. STATA software package [50] and MLwiN software version 2.1 [51] will be employed to handle the analysis.

Descriptive analysis of the adherence of health care providers to standard maternal and neonatal protocols will be done by cluster. Logistic regression will be applied to investigate the association between health provider adherence to protocols and the incidence of maternal and neonatal mortality. Responses from focus group discussions and key informant interviews will be manually transcribed, analyzed and grouped into various themes emphasizing the key convergent and divergent views that explain how and why the health care providers adhered, or did not adhere, to the intervention protocols.

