### Sample size estimation

This study is a superiority trial and has been designed and powered for neonatal mortality to contribute evidence for improved neonatal health care considering the predicted global upward trend in neonatal deaths [3] compared to maternal deaths. Two formulae were applied; the first formula was applied to estimate the required sample size in a randomized controlled trial (RCT) with binary outcome while the second formula was applied to inflate the estimated sample size for a CRCT. Neonatal mortality is the primary outcome, and is currently at approximately 30/1000 live births in the ER, Ghana. Evidence from previous studies including systematic reviews focusing on neonatal care interventions have shown a 23% to 51% reduction in neonatal mortality in settings including LIMC [39–44]. Our intervention will also address neonatal and maternal health care, hence we estimate an effect size of 30% on neonatal mortality with the use of this intervention. Intracluster correlation coefficient (ICC) for neonatal mortality in Ghana has been estimated at 0.0007256 [45]. To detect a 30% decline in neonatal mortality at a power of 80%, a significance level of 0.05 (two-tailed test), with a fixed number of eight clusters in each arm of the study, approximately 1065 patients in each of the 16 clusters will be needed. The first formula is:$$ m=\frac{n\left(1-\rho \right)}{\left( k- n\rho \right)}, $$where *m* = number of patients per cluster, *k* = number of clusters in each arms of the study, *ρ* = ICC and *n* = is the number of patients needed to detect this effect in a RCT. The second formula is:$$ n\kern0.5em =\kern0.5em \theta \left[\frac{\pi_{{}_{\mathbf{1}}}\left(1-{\pi}_{\mathbf{1}}\right)\kern0.5em +\kern0.5em {\pi}_{\circ}\left(1-{\pi}_{\circ}\right)}{{\left({\pi}_{\mathbf{1}}-{\pi}_{\circ}\right)}^2}\right] $$where *π*
_1_ = is the expected proportion of the neonatal mortality at the intervention group after RCT, *π*∘ = is the expected proportion of the neonatal mortality at the reference group after RCT and ϴ is the variance of the two proportions at a power of 80% and significance level of 0.05.

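### With 16 districts a propensity-score c-statistic cannot tell chance from imbalance, and adjusting for whatever imbalance is seen costs precision

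*Protocol article*

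**What the plan says.** The Statistical analysis section of the protocol article takes three linked steps.

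- Baseline characteristics of clusters and participants are described by arm, and the risk of imbalance among the clusters is assessed with the c-statistic of a propensity-score model.
- That statistic is defended as an "appropriate tool to detect baseline imbalance in CRCTs where sample size is large and when a large number of covariates are measured".
- The consequence follows: "Any observed imbalance in the baseline characteristics of clusters will be adjusted for in the statistical analysis". The next paragraph adds only that the logistic model will adjust for potential confounders.

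The Randomization section says "Sixteen clusters were, therefore, randomized". The Sample size estimation section puts eight in each arm and says that "approximately 1065 patients in each of the 16 clusters will be needed". The Data collection section lists the baseline variables: staffing and logistics, antenatal attendance, deliveries, obstetric and neonatal admissions, and all primary and secondary outcomes. Table 1 names ten outcome counts. Table 2 gives four facility counts per district by arm.

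**The concern.** Both the check and the adjustment rule concern characteristics of districts. A district characteristic takes 16 values, however many patients each district contributes, so the large-sample condition that the article attaches to its tool is not met. The other half of its justification, many covariates, makes matters worse: with 16 units, each added covariate raises the fitted c-statistic even under perfect randomization.

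The adjustment rule has a separate weakness. A covariate helps the primary analysis if it predicts neonatal mortality. Selecting covariates because they differ between arms selects those most correlated with treatment, whether or not they predict the outcome. A two-arm comparison of 16 clusters has 16 − 2 = 14 cluster-level degrees of freedom, and every such covariate spends one. At stake are the usefulness of the balance check and the precision of the primary estimate.

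**Working it through.** **1. The article's own design figure.** It states no c-statistic value or cut-off; its one computed figure is the cluster size. Inputs from Sample size estimation: control mortality "currently at approximately 30/1000 live births in the ER, Ghana"; "we estimate an effect size of 30% on neonatal mortality", so 0.030 falls to 0.021; ICC 0.0007256; 80% power; two-sided 0.05; k = 8.

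- n = (1.960 + 0.8416)² × [0.021×0.979 + 0.030×0.970] / 0.009² = 7.849 × 0.049659 / 0.000081 ≈ 4812 per arm.
- m = n(1 − ρ)/(k − nρ) = 4812 × 0.9992744 / (8 − 3.492) ≈ 1067, which agrees with 1065.

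The large sample is therefore 16 × 1065 = 17,040 patients; the number of districts is 16.

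**2. Chance c-statistic with 8 v 8 districts.** Independent noise covariates, logistic propensity model, apparent c-statistic, 1,500 runs per row:

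| Covariates | Median c | c ≥ 0.7 | c ≥ 0.8 | c = 1 |
|---|---|---|---|---|
| 1 | 0.61 | 18% | 4% | 0% |
| 2 | 0.67 | 41% | 12% | 0.1% |
| 3 | 0.73 | 66% | 26% | 1% |
| 5 | 0.81 | 88% | 56% | 10% |
| 6 | 0.88 | 96% | 73% | 23% |
| 8 | 1.00 | 99% | 92% | 62% |
| 10 | 1.00 | 99.9% | 99% | 93% |

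Mean c was about 0.73 with three covariates and 0.83 with five.

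**3. The trial's own districts.** Table 2 sums, intervention v control: hospitals 12 v 14, health centres 29 v 41, CHPS 28 v 41, maternity homes 4 v 6. Non-hospital facilities are thus 61 v 88. Entering the four counts gives c = 52/64 = 0.8125. Over all 12,870 possible 8:8 allocations of these districts the median is 50/64 = 0.78, and 40% of allocations reach 0.8125 or more. A value that looks like marked imbalance is an ordinary draw.

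**4. Participant-level sensitivity.** With 17,040 records and ten noise participant covariates (covariate ICC 0 to 0.05), median c is 0.51 to 0.60. At ICC 0.05, adding two, four or eight district covariates raises it to 0.70, 0.83 or 1.00.

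**5. Price of the adjustment rule.** Ten noise district covariates are taken as the assumed candidate list.

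- Adjusting where p<0.05 selects 10 × 0.05 = 0.5 covariates on average, and at least one in 1 − 0.95¹⁰ = 40% of trials.
- Adjusting where arms differ by more than 0.25 SD selects about 6, leaving about 14 − 6 = 8 degrees of freedom.

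An analytic guide: for q normal covariates unrelated to arm and outcome, the variance of the treatment effect is inflated on average by 13/(13 − q), and the t multiplier rises. For q = 6: √(13/7) = 1.363; t ratio 2.306/2.145 = 1.075; product 1.47. Six arbitrary covariates thus widen the interval by roughly 47%. Choosing them because they are imbalanced makes it somewhat worse.

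Simulation of cluster-level linear models agrees. With ten covariates, intervals were about 55% wider than unadjusted under the 0.25 SD rule and about 10% wider under p<0.05. Across 5 or 10 covariates, noise or prognostic, the 0.25 SD rule cost 10% to 57%; the penalty shrinks as the covariates become more prognostic. Type I error stayed between 3.8% and 5.4%.

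**The case against.** Several stronger readings are tempting, and the article does not support them.

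- *The check will flag imbalance almost always.* This needs a cut-off and a covariate count, and the article gives neither. At a cut-off of 0.7 it is true with about six or more district covariates (96% or more) but not with one or two (18% and 41%). Leaving such details to a fuller document is no fault in an article.
- *The propensity model has 16 rows.* The unit is not stated. The section also mentions participants, and the statement "Aggregate data on primary and secondary outcomes will be extracted from (DHIMS-2" does not settle it, since non-hospital outcomes are collected at facility level. With participant covariates only, the problem would not appear. What remains is that the check is worded as one of clusters, and a few district covariates restore the problem even in a patient-level model.
- *A high c-statistic triggers adjustment.* The article does not say so. The trigger is any imbalance observed, which is looser. The c-statistic results therefore do not measure the adjustment rule; step 5 does that separately.
- *Some characteristic will test significant.* With 20 characteristics tested at 5%, the chance is 1 − 0.95²⁰ = 64%. But the article plans description of baseline data, not significance tests, so this figure is only illustrative.
- *The result will be invalid.* Selection uses baseline values, not outcomes, and simulated type I error stayed near its nominal level. The fair charge is lost precision.

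**Conclusion.** The point stands as a stated rule that is worse than a cheap, widely accepted alternative. It is neither a missing detail nor a threat to validity. The c-statistic cannot separate chance from imbalance among 16 districts once several district covariates enter; the article's own Table 2 shows this, with 0.81 against a chance median of 0.78. The open-ended adjustment rule then spends scarce degrees of freedom on covariates picked for their association with arm.

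The size is conditional. The interval widening of about 10% (p<0.05) to about 55% (0.25 SD) assumes ten independent candidate covariates of no prognostic value and a cluster-level linear model standing in for the planned clustered logistic model. That the test keeps its level assumes small-sample degrees of freedom, which the article does not specify. The change should be made, but it is a matter of analysis wording.

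**What to change.** Delete the c-statistic step and the rule that any imbalance seen is adjusted for. Before outcome data are analysed, name one or two district-level covariates for the primary model, chosen for prognostic value:

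- first, each district's baseline institutional neonatal mortality rate, which the Data collection section already provides for;
- optionally, one facility-mix variable, justified by its expected relation to neonatal death. The observed 61 v 88 difference should not be the reason, since that would repeat the fault.

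Report the unadjusted clustered estimate beside the adjusted one, and present baseline characteristics descriptively.

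The cost is one or two of 14 degrees of freedom. By the guide in step 5, one wholly unprognostic covariate widens the interval by about √(13/12) × 2.160/2.145 = 1.05, or 5%, and two by √(13/11) × 2.179/2.145 = 1.10, or 10%. One covariate pays for itself once it explains about 1 − 1/1.048² = 9% of the variation between districts within arms. No new data are needed. The drawback is that chance imbalance in any other characteristic is handled only in a sensitivity analysis.

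### A significance-triggered adjustment for network availability, rated after the intervention and examined only in the intervention arm, is not kept out of the between-arm effect models

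*Protocol article*

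**What the plan says.** Three statements in the protocol article bear on this point.

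- **Statistical analysis, the effect model.** Effects on primary and secondary outcomes are to be "analyzed based on the principle of intention-to-treat to minimize over-estimation of the effect of the intervention". The model is a logistic regression that allows for clustering and adjusts for potential confounders.
- **Statistical analysis, later in the same paragraph.** Network connectivity is to be described for clusters in the intervention arm, and "any significant difference in network availability will be adjusted for using logistic regression". No model is named, no value is given for control clusters, and the adjusted analysis is not labelled secondary or exploratory.
- **Data collection.** "Availability of network connectivity in health facilities will be measured during the postintervention evaluation using a Likert scale administered to the health care providers". This sentence does not restrict measurement to one arm.

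For context, The intervention section says that phone reception may vary with facility location. The Discussion lists poor network as something that may limit providers' ability to use the system. The Randomization section says that masking was not feasible.

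**The concern.** The rule has three weak features.

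1. **One-arm use.** The variable is examined in the intervention arm only. Confounding of the arm comparison would need a difference between arms. The rule looks for differences inside one arm, so what triggers the adjustment is not what could justify it.
2. **Timing and source.** The score is collected after the intervention from unmasked providers, those in the intervention arm having used the system. Coverage may be a fixed feature of the site, but a rating of it could be coloured by experience with the system.
3. **A significance trigger.** Whether the adjustment is made depends on a test on post-randomisation data, so the estimand could change with the result of that test.

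If the adjustment enters the between-arm model, the reported effect is no longer the effect of being assigned the system under the network conditions that actually prevailed. It becomes the effect at one network level. If that level is good connectivity, the system is credited with what it achieves where the network works. That is the kind of over-estimation the intention-to-treat sentence is meant to limit.

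**Working it through.** **Inputs from the protocol article (Sample size estimation; Fig. 2).** Neonatal mortality is "currently at approximately 30/1000 live births in the ER, Ghana", so p0 = 0.030. A 30% reduction gives p1 = 0.021. Power is 80% and the two-sided significance level 0.05. The ICC is 0.0007256. Clusters were "randomized into eight control and eight intervention clusters". The stated size is 1065 per cluster.

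**Step 1. Reproduce the plan's own figure.**

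- n = (1.960 + 0.842)² × [p1(1−p1) + p0(1−p0)] / (p1−p0)² = 4812 per arm.
- m = n(1−ρ)/(k−nρ) = 4812 × 0.9992744 / (8 − 4812 × 0.0007256) = 1066.5 per cluster, against 1065 stated.

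The inputs are therefore read as the authors meant them. Nothing below changes this figure.

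**Step 2. Control clusters without a score.** In a complete-case fit every control record drops out. Among the remaining records the arm indicator is constant and duplicates the intercept, so the design has rank 2 for 3 parameters. The arm coefficient is not estimable.

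**Step 3. Control clusters given a fixed code c.** Assumptions, none of them from the article: a five-level score s = 1 to 5 spread evenly; an odds ratio of (0.021/0.979)/(0.030/0.970) = 0.694 at s = 3; a log-odds slope b per network step acting on the treatment effect; 8 × 1065 = 8520 births per arm; clustering ignored. The score varies in the intervention arm only, so its coefficient is estimated there, and the arm coefficient is the intervention-versus-control contrast at s = c:

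OR(c) = 0.694 × exp[b(c − 3)]

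| Control code | b = −0.1 | b = −0.2 |
|---|---|---|
| Network left out | 0.70 | 0.72 |
| c = 0 | 0.694 × e^0.3 = 0.94 | 0.694 × e^0.6 = 1.26 |
| c = 5 (maximum) | 0.694 × e^−0.2 = 0.57 | 0.694 × e^−0.4 = 0.46 |
| c = 3 (intervention-arm mean) | 0.69 | 0.69 |

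Fitted expected-count logistic models agree with these values. With c = 0 the standard error of the log odds ratio rises from about 0.10 to between 0.17 and 0.18.

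**Step 4. Cases that isolate the cause.**

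- Score recorded in both arms and unaffected by allocation: the odds ratio is unchanged (0.70 against 0.70).
- Score unrelated to outcome but used in one arm only: the odds ratio stays at 0.694, but the standard error rises to between 0.15 and 0.19 under the codes 5 and 0.

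The harm comes from using the covariate in one arm. Late measurement alone does not produce it.

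**Step 5. Dependence on the network distribution.** Assume a risk ratio of 0.70 with usable network and 1.00 without, and equal baseline risk.

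- Half of births without usable network: overall risk ratio 0.5 × 0.70 + 0.5 × 1.00 = 0.85. The arm coefficient would be 0.70 or 1.00 according to the reference level.
- 6% without: 0.94 × 0.70 + 0.06 × 1.00 = 0.718. With good network as reference the coefficient is again 0.70, so little is overstated.

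Trial status reports requests from 94% of participating facilities in the first six months. That counts facilities and not births, and a request does not prove reliable reception, but it sits closer to the second case than to the first.

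**The case against.** The strongest objection is that the article never says the adjustment enters the between-arm model. The opening reference to intervention-arm clusters can govern the whole sentence, and an analysis inside that arm has no treatment coefficient to distort. Logistic regression is not reserved for the randomised comparison either: the next paragraph uses it for the association between provider adherence and mortality. This stands as a possible reading, and the point is therefore conditional. It does not remove the point. The sentence sits in the paragraph on the intention-to-treat effect analysis, and the only effect named there that could be adjusted is that of the system. Nor is this detail merely left to a fuller plan, because the article states a rule and its trigger.

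A reader might infer more than the article supports:

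- **That the plan breaks intention-to-treat.** Adjusting for a covariate does not do so while every cluster is analysed as randomised, and nothing in the article excludes or reassigns a cluster.
- **That control clusters have no network score.** Data collection does not limit measurement to one arm; only the described analysis is limited.
- **That network availability is part of the intervention's effect.** The trial does not build coverage. The article ties reception to location, so it is largely a site characteristic and a possible effect modifier.
- **That the treatment coefficient would be uninterpretable.** It would be a level-specific effect, and with controls set at the intervention-arm mean it stays close to the unadjusted value. The difficulty is that the article fixes no coding.

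**Conclusion.** The point holds in conditional form. The article provides for a significance-triggered adjustment for a provider-rated, post-intervention variable examined in one arm, and does not say which model receives it. If it enters the effect model, the arm coefficient is either not estimable or set by the coding of control clusters, and it answers a different question from the effect of assignment.

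The illustrated odds ratios run from 0.46 to 1.26, against 0.70 to 0.72 without the variable. That range rests on the assumed slopes, the even five-level score, the coding and the neglect of clustering. With few poorly connected facilities and good network as reference the distortion could be small. If the adjustment stays within the intervention arm, the randomised comparison is untouched. Because the rule as written could alter the primary estimate, it should be settled before analysis.

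**What to change.** Replace the adjustment sentence with wording that:

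- states that the between-arm models for primary and secondary outcomes exclude network availability;
- removes the significance trigger;
- limits the variable to description, or to an analysis within the intervention arm labelled exploratory.

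If the sponsor wants to know whether the effect varies with connectivity, use a measure collected the same way in both arms, preferably one that cannot be influenced by allocation, and test an arm-by-network interaction in a separate, labelled analysis.

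The main change costs one sentence. It needs no new data and leaves the sample size as it is. Only the optional interaction analysis would need the score from control facilities, if it is not already collected there.
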